**Discussion::**

Our study results will provide evidence of the efficacy and safety of thread embedding acupuncture combined with conventional acupuncture for the management of chronic low back pain. Even though the assessors will be blinded, the patients will not be blinded to treatment because of the lack of a sham embedding acupuncture group; this is a limitation of our study.

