### Objectives

2.1

The aim of this study was to examine the efficacy and safety of TEA combined with conventional acupuncture for chronic low back pain through comparisons with the effects of conventional acupuncture alone

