### Sample size calculation

2.14

Sample size calculation was performed to determine the appropriate number of participants. The primary outcome will be the change in the VAS score from visit 1 to visit 16 in the treatment and control groups. To our knowledge, no study has investigated the effects of TEA combined with conventional acupuncture treatment. A previous clinical trial evaluated the effects of TEA and sham TEA administered for 4 weeks.^[24]^ The change in the VAS score after treatment (week 4) was 1.85 ± 0.86 in the treatment group and 0.5 ± 0.80 in the control group. The required number of participants per group was 11, considering a 2-tailed test with a 1:1 allocation ratio, a superiority trial, a test power of 95% (1-β), and a significance level of 5% (α). After considering a 40% dropout rate, we calculated the sample size for our study to be 19 patients per group. Thus, a total of 38 participants will be required.

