### Statistical analysis

2.15

Data will be expressed as means and standard deviations for continuous variables and frequencies and ratios (%) for categorical variables. The patients’ baseline characteristics will be compared using an independent *t* test or the Wilcoxon rank-sum test for continuous variables and a χ^2^ test or Fisher exact test for categorical variables. If there is a significant difference in the baseline characteristics between groups, analysis of covariance will be used for efficacy analysis, which will include both a full analysis set (FAS) and a per-protocol set (PPS). FAS will be used for the main analysis and PPS will be used for subanalysis of sensitivity. FAS will include patients who will receive at least 1 session of treatment and will undergo at least 1 pain assessment using VAS after treatment. FAS will not include participants who do not meet the eligibility criteria, those who do not receive any treatment, or those whose data are not acquired after randomization. PPS will include patients who will receive at least 12 sessions of treatment (75% compliance rate), those who undergo pain assessment using VAS at visit 16, and those who will complete the clinical trial without major protocol violation. In the primary outcome analysis, the change in the VAS score from visit 1 to visit 16 will be compared between the treatment group and the control group using an independent *t* test or the Wilcoxon rank-sum test according to normality. In the secondary outcome analysis of continuous variables, a *t* test or the Wilcoxon rank-sum test will be applied according to normality. In the secondary outcome analysis of categorical variables, a χ^2^ test or Fisher exact test will be applied. In safety analysis, the total adverse event ratio and adverse event ratio associated with TEA will be compared using a χ^2^ test or Fisher exact test. The last observation carried forward method will be used for missing data. The level of significance will be 5% (2-tailed test). No correction method will be applied for multiple comparisons in the secondary outcome analysis.

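### The only planned between-arm safety comparison is a 5% significance test in 19 patients per arm, which cannot by itself support the evidence of safety that the article promises; a risk difference with a confidence interval would serve better

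*Protocol article*

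**What the plan says.** Section 2.1 of the protocol article names safety as an aim: "The aim of this study was to examine the efficacy and safety of TEA combined with conventional acupuncture". The Discussion part of the abstract goes further: "Our study results will provide evidence of the efficacy and safety of thread embedding acupuncture combined with conventional acupuncture". The closing Discussion (section 3) repeats that expectation.

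The between-arm safety analysis is one sentence in section 2.15: "In safety analysis, the total adverse event ratio and adverse event ratio associated with TEA will be compared using a χ^2^ test or Fisher exact". The same section sets a two-sided 5% significance level for the analyses in general. It names no interval, margin or upper bound for the adverse event difference.

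The sample size in section 2.14 rests on the VAS change only: "The required number of participants per group was 11, considering a 2-tailed test with a 1:1 allocation ratio". It is then inflated: "After considering a 40% dropout rate, we calculated the sample size for our study to be 19 patients per group".

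Section 2.12 plans the safety data: examinations, vital signs and adverse event checks at every visit, blood tests at visits 1 and 16, assessment by RCTC v2.0, and calculation of the adverse event ratio. Section 2.15 adds frequencies and percentages for categorical variables.

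**The concern.** The null hypothesis of a χ² or Fisher test is that the arms have the same event rate. Rejecting it can show a difference. Not rejecting it shows nothing unless the test had a good chance of rejecting when harm was present. A trial sized on a large expected pain effect may have little such chance for adverse events, where the effect may be smaller and the outcome is binary.

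At stake is what the trial can say about one of its two aims. If the comparison between arms rests on this p value, a material increase in patients with adverse events and no increase at all can lead to the same non-significant result.

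This point concerns the total adverse event ratio, where both arms can have events. The test of TEA-associated events is a separate matter, because control patients receive no TEA.

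**Working it through.** **1. The plan's own figure.** Inputs from section 2.14: VAS change 1.85 ± 0.86 versus 0.5 ± 0.80, two-sided 5%, power 95%, 1:1 allocation, 40% dropout.

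- Difference: 1.85 − 0.5 = 1.35.
- Pooled SD: √((0.86² + 0.80²)/2) = 0.8305.
- Two-sample t test power (noncentral t): 93.0% at 10 per arm and 95.2% at 11 per arm, so 11 are needed.
- Dropout: 11/(1 − 0.40) = 18.3, rounded up to 19 per arm, 38 in total.

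The stated size reproduces. No adverse event rate enters it.

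**2. Miss rate of the adverse event test.** The article gives no adverse event rates, so the rates below are assumptions, shown over a range. Let X and Y be the numbers of patients with at least one event in the TEA and control arms, independent binomials with n = 19.

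Miss rate = 1 − Σ P(X = x) · P(Y = y), summed over all tables (x, y) with p < 0.05.

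The sum was enumerated exactly over all 20 × 20 tables.

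| Control vs TEA arm (assumed) | Missed, Fisher | Missed, uncorrected χ² |
|---|---|---|
| 5% vs 15% | 94% | 86% |
| 10% vs 30% | 78% | 66% |
| 20% vs 40% | 82% | 72% |
| 30% vs 60% | 63% | 52% |
| 20% vs 60% | 35% | 24% |
| 25% vs 75% | 16% | 10% |

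The two doublings in the table are missed more often than not by either test. A tripling is missed in most trials at a low control rate, but usually detected once the control rate reaches 20%.

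**3. What the p value hides.** Take 6/19 versus 2/19 patients with an event.

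- Fisher, two-sided: p = 0.23.
- Risk difference: 6/19 − 2/19 = 0.316 − 0.105 = 0.211.
- Wilson 95% limits: 0.154 to 0.540 for 6/19; 0.029 to 0.314 for 2/19.
- Newcombe lower limit: 0.211 − √((0.316 − 0.154)² + (0.314 − 0.105)²) = −0.05.
- Newcombe upper limit: 0.211 + √((0.540 − 0.316)² + (0.105 − 0.029)²) = +0.45.

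The result is not significant, yet it is compatible with an excess of 45 percentage points.

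**4. How many events are needed for significance.** Against 2/19 in controls, Fisher needs 9/19 in the TEA arm (8/19 gives p = 0.062). Uncorrected χ² needs 8/19 (p = 0.027). The threshold therefore depends on which of the two tests is used.

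**5. Zero events.** With 0/19 patients having a given event, the exact two-sided 95% upper limit is 1 − 0.025^(1/19) = 0.176. A true rate of up to 17.6% is not excluded.

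**The case against.** The strongest reply is that the article contains no misuse. Nowhere does it say that p > 0.05 will be read as safety. A reader might infer that rule from the promise of safety evidence together with the test, but the text does not support the inference: section 2.15 says only that the ratios will be compared. This part of the reply stands.

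A reader might also infer that safety is judged by this test alone. That is not supported either. Section 2.12 plans adverse event ratios, graded events, examinations, vital signs and blood tests, and section 2.15 also tests TEA-associated events. What remains true is narrower: for all adverse events together, the arms are compared only by the test.

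A third tempting reading is that a tripling of events would be missed about three times in four. This holds only near an assumed control rate of 10% (66% to 78%, by test). At 20% versus 60% the miss rate is 24% to 35%, and at 25% versus 75% it is 10% to 16%. All patients receive 14 needles at 16 sessions with events checked at each visit, so a control rate above 10% cannot be ruled out. Nor should 11 per arm be used as the safety denominator: it is the number required for the VAS test, and patients who drop out still contribute the events recorded before they left.

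Finally, an interval for the risk difference is often left to a statistical analysis plan, and the article states none for efficacy either. This has weight. But the article does not leave the safety comparison open: it names the method, and it promises evidence that a test of no difference cannot supply at this size. Low power for harm is common in small trials, which is a reason to report estimates and not tests.

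**Conclusion.** The point holds in a limited form. The one between-arm comparison planned for total adverse events is a significance test in a trial sized on VAS, and a non-significant result from it could not support safety. That follows from the form of the test and needs no assumed rate.

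The size of the problem does depend on assumed rates. With 19 per arm the miss rate runs from 94% (Fisher, 5% versus 15%) down to 10% (χ², 25% versus 75%). The calculation assumes independent patients, one yes-or-no outcome per patient, and all 19 per arm in the safety analysis.

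The primary efficacy analysis is unaffected, and the safety data to be collected are adequate for the remedy. This is a cheap improvement, not an error that invalidates the plan.

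**What to change.** In section 2.15, for the total adverse event comparison:

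- Make the main summary the number and proportion of patients with at least one adverse event in each arm, and the risk difference (TEA plus acupuncture minus acupuncture alone) with a 95% confidence interval, Newcombe or exact, naming which.
- Treat any χ² or Fisher p value as descriptive, and say that a non-significant difference will not be taken as evidence of safety.
- Word the safety conclusion as an estimate with its upper limit, and keep the statements in the abstract and section 3 in line with that.

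The cost is a few lines of text and one interval computed from data already to be collected, with no extra patients, visits or procedures. The downside is a more modest safety claim: the interval will be wide, and the report will have to say so.

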**Methods::**

This randomized, controlled, assessor-blinded, 2-armed, parallel, multicenter clinical trial will include 38 outpatients with chronic low back pain recruited from 4 traditional Korean Medicine hospitals. The patients will be randomly allocated to a treatment group (conventional acupuncture + thread embedding acupuncture) and a control group (only conventional acupuncture) in a 1:1 ratio. The treatment group patients will receive thread embedding acupuncture treatment at 10 acupuncture points (multifidus muscle, 4 points; spinal erector muscles, four points; lumbar quadrate muscle, 2 points) once a week for 8 weeks (8 sessions). In addition, all patients will receive conventional acupuncture treatment at 14 acupuncture points (GV3, EX-B5, and bilateral BL23, BL24, BL25, BL26, BL40, and BL60) twice a week for 8 weeks (16 sessions). The primary outcome will be the change in the visual analog scale score from visit 1 to visit 16, analyzed by independent *t* tests, in both groups. The groups will also be compared with regard to the clinical relevance (minimal clinically important difference), quality of life (3-level version of Euroqol-5D), disability level (Roland and Morris Disability Questionnaire), global assessment (patient global impression of change), and safety. Cost data for cost–benefit and cost-effectiveness analyses will be collected.

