#### Study schedule

2.9.1

The study schedule is presented in Table 1. The trial will include a screening phase, treatment phase, and follow-up phase. At the screening visit, participants will sign the informed consent form. The investigator will perform a physical examination, record the medical history, obtain an L-spine X-ray, collect blood samples, record any concomitant treatment history, and use VAS to determine whether the participant is eligible for the clinical trial. If the participant is taking anti-inflammatory drugs or pain killers, we will implement a 2-week washout period. During the 8 weeks of treatment, the patient will visit the facility twice a week (16 visits). Conventional acupuncture treatment will be administered at every visit in both the treatment group and the control group. Eight sessions of TEA will be conducted once a week only in the treatment group (visits 1, 3, 5, 7, 9, 11, 13, 15). On visits 17, the participants will visit the facility 12 weeks after visit 16. VAS scores for pain will be determined on visits 1, 4 (week 2), 8 (week 4), 12 (week 6), 16 (week 8), and 17 (week 20).

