**Figure 2 F2:**
[figure not shown]
Point location and direction of thread embedding acupuncture for patients with chronic low back pain. (1) Multifidus muscle: Perpendicular insertion at EX-B2 points positioned on either side of L4–5 (n = 2) and L5-S1 (n = 2). (2) Spinal erector muscles: Transverse insertion at points located 3–4 cm from the L3 (one on each side, n = 2) and S1 spinous processes (one on each side, n = 2), toward L1. The thread will be located in the shallow muscle layers. (3) Lumbar quadrate muscle: Transverse insertion at 2 points, from the L4 spinous process toward the bilateral iliac crest. The thread will be located in the shallow muscle layers.

In the treatment group, conventional acupuncture treatment will be administered immediately after TEA. Sterilized stainless steel needles (DB108C; Dongbang Medical Co., Boryung-si, South Korea) measuring 0.25 mm in width and 40 mm in length will be inserted at 10 local and 4 distal acupuncture points. The 10 local acupuncture points are as follows: GV3, EX-B5, and bilateral BL23, BL24, BL25, and BL26. The 4 distal acupuncture points are as follows: bilateral BL40 and BL60. Details about the treatment group intervention are described in the Standards for Reporting Interventions in Clinical Trials of Acupuncture (STRICTA) checklist in Table 2.^[17]^

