#### Control group intervention

2.9.3

The control group patients will receive conventional acupuncture treatment following the same protocol used for the treatment group. TEA will not be administered.

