This study has several strengths. First, experienced practitioners will provide TEA treatment, thus enhancing the quality of trial data. Second, the multicenter setting will prevent bias. Third, we will evaluate not only the pain intensity but also the clinical relevance, quality of life, disability level, global assessment, and costs. Fourth, we will examine the effects of TEA combined with conventional acupuncture, which reflects an actual clinical setting. However, several limitations also exist. First, we calculated the sample size on the basis of a study with a protocol different from the presently described one; the treatment duration in the previous study was only 4 weeks,^[24]^ whereas that in our study is 8 weeks. Therefore, we could have overestimated the sample size. Second, the previous study^[24]^ compared actual TEA with sham TEA; participants were accordingly blinded to the allocated group. In this study, no TEA will be used in the control group, so the participants and practitioners will not be blinded to the allocated group. This could influence the results of the study. Finally, we have not specified any rescue drugs, which could result in an increased dropout rate due to severe pain. Nevertheless, the study design is ideal to determine the precise therapeutic effects of TEA. Despite the limitations, the findings of this trial are expected to provide evidence about the efficacy and safety of TEA for chronic low back pain, which will be useful for physicians, stakeholders, patients, and researchers.

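### The planned test of TEA-associated adverse events has a control proportion that is zero by design, so it is not a valid between-arm contrast

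*Protocol article*

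**What the plan says.** Section 2.15 of the protocol article plans two safety comparisons in one sentence: "In safety analysis, the total adverse event ratio and adverse event ratio associated with TEA will be compared using a" χ² or Fisher exact test. The same section sets the level: "The level of significance will be 5% (2-tailed test"). The sentence does not name the groups, but the trial has two arms and the abstract lists safety among the outcomes in the statement that begins "The groups will also be compared with regard to the clinical relevance".

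Exposure to TEA is fixed in three places.
- Study schedule (2.9.1): "Eight sessions of TEA will be conducted once a week only in the treatment group".
- Control group intervention (2.9.3): "TEA will not be administered".
- Discussion: "In this study, no TEA will be used in the control group, so the participants and practitioners will not be blinded to the allocated group". The abstract also states that there is no sham embedding group.

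Conventional acupuncture is given to both arms at all 16 treatment visits. At a visit with TEA, section 2.9.2 says that "conventional acupuncture treatment will be administered immediately after TEA".

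**The concern.** A between-arm test of proportions asks whether two groups that could both have the event have it equally often. A control patient treated as allocated cannot have an event caused by TEA, because nothing resembling TEA is done to that patient. The control cell is known before the trial starts, and the hypothesis of equal proportions is false as soon as TEA causes a single event. The test therefore adds nothing to the treatment-arm count.

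It also leaves out the comparison that a reader would want. Both procedures are applied to the low back, so bruising or soreness there can follow either one. In the treatment arm such an event may be labelled TEA-associated; in the control arm it can only be put down to needling and does not enter this ratio.

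Safety stands beside efficacy in the stated aim (section 2.1). A p value above 0.05 on this line could be read as no excess harm from TEA, and one below 0.05 as an excess over needling. The test supports neither statement.

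**Working it through.** **Inputs.** Arm size 19 and allocation 1:1 from section 2.14; two-sided 5% level from section 2.15; control count 0 from sections 2.9.1 and 2.9.3 and the Discussion. The event counts below are a range of possible results, since the article gives no expected rate.

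**1. The plan's own figure.** Section 2.14 specifies "considering a 2-tailed test with a 1:1 allocation ratio, a superiority trial, a test power of 95% (1-β), and a significance level of 5% (α"), with changes of 1.85 (SD 0.86) and 0.5 (SD 0.80).
- Difference: 1.85 − 0.5 = 1.35. Pooled SD: √[(0.86² + 0.80²)/2] = 0.8305.
- The noncentral t distribution gives power 0.930 at 10 per group and 0.952 at 11, so 11 per group reproduces.
- 11/(1 − 0.40) = 18.3, rounded up to 19 per group, 38 in total. This also reproduces, so 19 is the right arm size for the safety test.

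**2. The p value with the control arm at zero.** For x of 19 against 0 of 19, the margins are equal and the two-sided Fisher value is p = 2 × C(19, x) / C(38, x). No control-arm observation enters it.

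| TEA-arm patients with event | Calculation | Fisher p | χ² p, uncorrected |
|---|---|---|---|
| 1 (5%) | 2 × 19/38 | 1.000 | 0.311 |
| 2 (11%) | 2 × 171/703 | 0.487 | 0.146 |
| 3 (16%) | 2 × 969/8,436 | 0.230 | 0.071 |
| 4 (21%) | 2 × 3,876/73,815 | 0.105 | 0.034 |
| 5 (26%) | 2 × 11,628/501,942 | 0.046 | 0.016 |
| 6 (32%) | 2 × 27,132/2,760,681 | 0.020 | 0.008 |

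Fisher crosses 5% at 5 patients and the uncorrected χ² at 4. With counts this small the expected cells are below 5 (4 events give 2 expected per arm), so Fisher is the usual choice of the two.

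**3. How often Fisher would reject.** This is P(X ≥ 5) with X binomial(19, π). The true rates π are assumptions, not figures from the article.

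| Assumed true rate | 5% | 10% | 20% | 30% | 40% |
|---|---|---|---|---|---|
| Chance of p < 0.05 | 0.2% | 3.5% | 33% | 72% | 93% |

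If one patient in five had a TEA-caused event, the test would be non-significant about two times in three.

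**4. Why the needling rate does not enter.** Suppose 5 of 19 treated patients have local bruising attributed to TEA and 5 of 19 controls have the same bruising after needling, with no other events. The TEA-associated test compares 5/19 with 0/19 and gives p = 0.046. Events related to any study procedure are 5/19 against 5/19: risk difference 0, Fisher p = 1. The same patients give opposite messages.

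**5. What a descriptive report would show.** Clopper-Pearson 95% limits for x of 19 are the 2.5% point of Beta(x, 20 − x) and the 97.5% point of Beta(x + 1, 19 − x).
- 3/19: 3.4% to 39.6%
- 4/19: 6.1% to 45.6%
- 5/19: 9.1% to 51.2%

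The intervals for 4 and 5 events nearly coincide, although the test labels them differently.

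**The case against.** **The valid comparison is already planned.** The sentence begins with the total adverse event ratio, to which both arms can contribute. This stands. The safety aim does not hang on the faulty test, and a reader who inferred that the whole safety analysis is unsound would go beyond the text.

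**The zero depends on a reading.** Section 2.15 neither defines association with TEA nor says between which groups the ratio is compared, and section 2.12 speaks more broadly of events linked to the intervention. If that broader category was meant, controls can contribute and the zero disappears. This stands as a possibility, but section 2.15 names TEA, so the wording needs correcting on either reading.

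**The p value does track harm.** A reader might infer that it says nothing about harm, or that significance would come purely from the definition. Neither holds: p falls as the treatment-arm count rises, and p < 0.05 by Fisher needs at least 5 of 19 patients with an attributed event. The fault is that p carries no information beyond that count and the arm size.

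**Attribution is not shown to be biased.** A reader might infer that causality will be judged by people who know the arm. The article leaves practitioners unblinded but does not say who judges causality; section 2.8 blinds the assessor, data collector and statistician. In addition, TEA is given only at odd-numbered visits and needling at every visit, which helps to separate the two within the treatment arm. Difficulty of attribution is a separate matter and would also affect a descriptive report.

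**Small arms explain the wide uncertainty.** True. The width of the exact intervals reflects 19 patients per arm and is not a measure of this defect.

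**Conclusion.** The point holds for one of the two planned safety tests. Read as a between-arm comparison of events attributed to TEA, the test has a control proportion of zero by design and is not a valid contrast. At 19 per arm, up to 4 of 19 patients (21%) with such an event reads as non-significant by Fisher (p = 0.105) and 5 of 19 (26%) as significant (p = 0.046), regardless of how often similar local events follow needling alone.

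This assumes that controls are treated as allocated, that all 19 per arm enter the safety analysis (the article gives no separate safety set), and that Fisher is used. At 11 per arm the Fisher threshold is still 5 patients.

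The total adverse event comparison, the primary analysis and the sample size are unaffected. The correction should be made because this line could be misread on a stated aim of the trial.

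**What to change.** In section 2.15:
1. Drop the between-arm test of TEA-associated events. Report them in the TEA arm only, as patients with an event and a percentage, with an exact (Clopper-Pearson) 95% confidence interval and no p value.
2. Keep the between-arm comparison of all adverse events, and add one of events related to any study procedure, TEA or conventional acupuncture. Preferably give each as a risk difference with a 95% confidence interval.
3. If the TEA-associated ratio was intended to mean events linked to the intervention, as in section 2.12, reword section 2.15 to say so and state that it covers both procedures.

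The cost is a small change in analysis wording, with no effect on sample size or visits. The case report form must record relatedness to any study procedure. Section 2.12 says that events are recorded and assessed there but describes no such field, so this should be checked; if it is absent, it has to be added and completed for patients already enrolled, since recruitment is under way.

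### LOCF is the only missing-data rule for the primary analysis, although the plan allows for 40% dropout and concedes that severe pain could raise it

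*Protocol article*

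**What the plan says.** The Statistical analysis section (2.15) gives one rule for missing values: "The last observation carried forward method will be used for missing data". The primary comparison is the VAS change from visit 1 to visit 16, by t test or Wilcoxon test. The main analysis uses the full analysis set (FAS), which needs one treatment session and one later VAS. The per-protocol set (PPS) serves as sensitivity analysis and requires a visit-16 VAS.

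The Sample size calculation (2.14) states: "After considering a 40% dropout rate, we calculated the sample size for our study to be 19 patients per group". It gives no reason for the 40%. The Discussion lists as a limitation that "we have not specified any rescue drugs, which could result in an increased dropout rate due to severe pain".

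Four other places bear on the point:
- Study schedule (2.9.1): VAS is taken at visits 1, 4, 8, 12 and 16 (weeks 2, 4, 6 and 8 for the last four) and at visit 17, which falls 12 weeks after visit 16.
- Concomitant treatment (2.9.4): the ban on other treatments covers the 8 treatment weeks but not follow-up.
- Blinding (2.8): patients and practitioners know the allocation.
- Subject withdrawal criteria (2.6): one criterion counts TEA sessions, which only the treatment arm receives.

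**The concern.** LOCF assumes that a patient's pain stays where it was at the last visit, and it then analyses the filled-in value as if it had been measured. Pain is expected to fall over an 8-week course, so a week-2 score is generally not a week-8 score. A patient who leaves because of pain may also be worse at week 8 than the last recorded score suggests. The first error understates that patient's gain and the second overstates it, so the between-arm contrast can move either way.

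The plan leaves room for this to matter. The dropout allowance is large, and open allocation and a withdrawal criterion tied to TEA sessions make unequal dropout plausible. The two sections also treat dropouts differently: the sample size counts them as lost, while the analysis counts those with one later VAS as fully observed, so the standard error ignores the uncertainty of the imputed values.

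The secondary week-20 comparisons are affected too. A missing visit-17 score would be replaced by week-8 pain, carried across 12 weeks in which other treatments are allowed.

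**Working it through.** **1. The plan's own figure.** Section 2.14 takes changes of "1.85 ± 0.86 in the treatment group and 0.5 ± 0.80 in the control group" from an earlier 4-week study of TEA against sham TEA.
- Difference: 1.85 − 0.5 = 1.35.
- Pooled SD: √((0.86² + 0.80²)/2) = 0.8305.
- Standardised effect: 1.35/0.8305 = 1.625.
- With two-sided 5% and 95% power, the exact t calculation gives power 0.930 at 10 per group and 0.952 at 11. This agrees with the plan ("The required number of participants per group was 11").
- Inflation: 11/(1 − 0.40) = 18.3, so 19 per group and 38 in total. The stated sample size reproduces.

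**2. How many primary values could be carried forward.** 0.40 × 19 = 7.6, about 8 per arm and about 15 of 38 overall. Within the allowance this is an upper bound, because patients with no post-treatment VAS leave the FAS.

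**3. Assumptions for the bias (not from the documents).**
- The planning figures carry no unit and refer to week 4. They are read here as 18.5 and 5 mm at week 8, with SD 8.3 mm; SD 20 mm is a second case.
- Improvement is linear, so weeks 2, 4 and 6 show 0.25, 0.5 and 0.75 of the week-8 change.
- Dropouts are spread evenly after visits 4, 8 and 12, so the mean fraction is 0.5.

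**4. Equal dropout, improvement would have continued.** With 8 of 19 dropouts per arm, LOCF estimates 13.5 × (11 + 8 × 0.5)/19 = 10.66 mm. The loss is 2.84 mm, or 21%.

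**5. Equal dropout, dropouts relapse to baseline.** At 40% per arm the true contrast is 0.6 × 13.5 = 8.1 mm. LOCF gives 8.1 + 0.4 × f × 13.5, which is 9.45, 10.8 or 12.15 mm for f = 0.25, 0.5 or 0.75. The effect is now overstated by 1.35 to 4.05 mm.

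**6. No true difference, unequal dropout.** Both arms improve by 18.5 mm; 5/19 drop out in one arm and 10/19 in the other. The LOCF difference is 18.5 × (10 − 5) × 0.5/19 = 2.43 mm in favour of the arm with fewer dropouts. The sign reverses if the dropout pattern is swapped.

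**7. Effect on the test.** Simulation with 20,000 replicates, 19 per arm, within-patient correlation 0.7, fixed dropout counts unrelated to pain:

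| True difference | Dropouts | LOCF difference | Rejection, SD 8.3 mm | Rejection, SD 20 mm |
|---|---|---|---|---|
| 13.5 mm | 8 v 8 | 10.7 mm | about 95% (power) | – |
| 0 | 8 v 8 | 0 | about 2.8% | about 4.6% |
| 0 | 7 v 9 | about 0.9 mm | about 3.6% | about 4.7% |
| 0 | 5 v 10 | about 2.4 mm | about 9% | about 5.7% |

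Rates below 5% partly reflect the fixed counts: the spread between dropout times enters the estimated SD, but the number of dropouts never varies.

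**8. Other trajectory.** With front-loaded improvement (fractions 0.5, 0.7, 0.85) the mean shortfall is 1 − 2.05/3 = 0.317. The bias in step 6 becomes 18.5 × 5/19 × 0.317 = 1.54 mm, with rejection about 7% at SD 8.3 mm.

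**9. Dropout driven by poor response.** A separate simulation let a poor VAS response raise the chance of leaving, with no true effect. With about 23% against 60% dropout, the LOCF contrast was about 0.43 on the planning scale in either direction and rejection about 27%. With about 41% in both arms, rejection stayed at about 5%. The 23% and 60% are chosen to show the mechanism; the documents give no arm-specific rates.

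**The case against.** Several points against the concern are sound.

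- A reader might infer that the plan expects 40% of patients to leave because of pain. It does not say so. The 40% is a sample-size allowance without a stated cause, and the Discussion says only that pain-related dropout could rise.
- A reader might infer that LOCF inflates type I error in this trial. With no true effect, equal dropout and equal trajectories it does not. With 7/19 against 9/19 the rate is still below 5%. Inflation needs a marked imbalance and shrinks at SD 20 mm.
- In the planning scenario the bias is conservative and power stays near the 95% target. A spurious 2.4 mm is also far below the 20 mm that section 2.11.2 takes as clinically important.
- The plan is not without a sensitivity analysis. In the scenarios of steps 4 and 6, where dropout is unrelated to pain, a visit-16 completers comparison returns 13.5 mm and 0 mm, so the PPS would expose the LOCF bias.
- Further missing-data sensitivity analyses may stand in a statistical analysis plan that is not shown. Their absence from an article is not the point raised here.

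What remains is the stated rule itself. It governs the primary contrast, and the plan gives no assurance that dropout will be equal. A true effect is attenuated even when dropout is equal and improvement would have continued. The PPS, being limited to completers, does not protect against pain-driven dropout, the mechanism that the Discussion itself raises.

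**Conclusion.** The point holds as a should-fix. LOCF as the sole method for the FAS main analysis is a weak choice under a 40% dropout allowance with pain-related dropout acknowledged as possible.

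Under the stated assumptions a true 13.5 mm is reported as about 10.7 mm with 8/19 dropouts per arm. With no true difference and 5/19 against 10/19, a difference of about 2.4 mm appears in either direction, with type I error about 9% at SD 8.3 mm and about 5.7% at SD 20 mm. If dropouts relapse, the effect is overstated instead.

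These sizes depend on the assumed linear course, on the conversion of unitless week-4 figures from a TEA-against-sham study, and on assumed dropout patterns. That bias is possible in both directions is well supported; its size in this trial cannot be known from the documents. They do not support saying that the primary result will be biased, or that the dropout is expected to be pain-related.

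**What to change.** - **Primary analysis.** Replace LOCF by a likelihood-based repeated-measures model on the VAS at visits 4, 8, 12 and 16, with treatment, visit, treatment-by-visit, baseline VAS and hospital. The visit-16 contrast is the primary estimate. The model uses every recorded score without freezing dropouts at the last one.
- **Sensitivity.** The model assumes data missing at random and can itself be biased if dropout depends on unrecorded pain. Add one delta-adjusted or control-based imputation analysis in which dropouts fare worse. Keep the PPS, and keep LOCF only as supportive.
- **Week 20.** Do not carry week-8 pain forward to visit 17; the same model can include that visit.
- **Cost.** A change of wording and modest programming. The visits are already scheduled and the sample size of 38 need not change. The downside is a few more parameters at this size: an unstructured covariance over four visits has 4 × 5/2 = 10, so a small-sample degrees-of-freedom correction such as Kenward-Roger should be named.
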